## Abstract

**Background:**

Atopic dermatitis (AD) is a chronic relapsing skin disease that has long-term physical and mental health impacts on children with this condition. Current treatments mainly include anti-inflammatory, antibacterial, and anti-allergic interventions, systemic therapy, and recently emerging target-focused agents. However, these treatments have limited effectiveness and unwanted side effects. The use of traditional Chinese medicine (TCM) in the treatment of AD has a long history, with promising efficacies, low toxicity, and improvements in the quality of life of patients with AD. Longmu Tang granule, a TCM, has been used to effectively treat AD since 2008 through doctors’ prescriptions. To scientifically evaluate the clinical efficacy and safety of Longmu Tang granule, we proposed to launch a single-centred, double-blinded, randomised, placebo-controlled trial.

**Methods:**

In this single-centred, double-blinded, randomised, placebo-controlled clinical trial conducted at Xiyuan Hospital of China Academy of Chinese Medical Sciences, a total of 60 participants will be randomly assigned (1:1) to receive the Longmu Tang granule or placebo granule for 8 weeks. The primary outcome will be evaluated using the index of Scoring Atopic Dermatitis. The secondary outcomes will be evaluated using the Children’s Dermatology Life Quality Index and the number cancellation test. The mechanistic evidence will be the serum levels of inflammatory cytokines, including immunoglobulin E, tumour necrosis factor-α, interleukin-1, and interleukin-6.

**Discussion:**

The results of this trial will provide evidence of the efficacy and safety of the Longmu Tang granule and prove its anti-inflammatory action in patients with AD.

**Trial registration:**

Chinese Clinical Trial Registry Chictr.org ID: ChiCTR2100041591. Registered on 1 January 2021

## Administrative information

Note: the numbers in curly brackets in this protocol refer to SPIRIT checklist item numbers. The order of the items has been modified to group similar items (see http://www.equator-network.org/reporting-guidelines/spirit-2013-statement-defining-standard-protocol-items-for-clinical-trials/).

## Introduction

### Background and rationale {6a}

Atopic dermatitis (AD) is one of the most common chronic relapsing skin diseases and is characterised by severe itching, papules, dryness, exudation, and scarring in infants, children, and adults [1]. A recent epidemiological study showed that the prevalence of AD was as high as 10–20% in developed countries [2]. AD affects up to 12.94% of children aged 1–7 years in 12 cities in China [3]. AD is not only associated with food allergies, asthma, allergic rhinitis, and other immune-mediated inflammatory diseases; recent literature also suggests AD is associated with attention-deficit/hyperactivity disorder (ADHD) and mental health disorders, such as depression [4–7]. The typical clinical features of AD are intensive pruritic and eczematous dermatitis that can severely affect quality of life. AD has a greater impact on children's quality of life than other chronic childhood diseases, including asthma and type 1 diabetes [8]. Families and caregivers experience significant stress and high expenditures because of difficult and time-consuming treatments [9]. Thus, AD is associated with substantial distress, reduced quality of life, and increased resource demands for families.

Although the underlying pathogenesis of AD is not fully understood, it is known to be caused by complex interactions of abnormal barrier function, cutaneous microbiome invasion, and predominantly type-2-skewed immune dysregulation [10]. AD lesions show destruction of the skin barrier caused by inflammatory cytokines from T helper 2 cell-mediated immunity. Patients with mild-to-moderate AD develop red, oozing, and crusted rashes, which have chronic recurrence and may be limited to the face, scalp, hands, arms, feet, or legs. Pruritus is the major subjective symptom, and it causes frequent scratching, which may exacerbate the itch-and-scratch cycle and result in secondary skin infections. Pruritus and frequent scratching at night cause difficulty in falling asleep and affect the quality of life. Lack of sleep at night and early waking can induce adverse consequences in children with AD, such as psychological disorders, inattention, behavioural changes, and difficulty in remembering daily affairs. Thus, there is a need to search for more effective novel therapeutic strategies to alleviate chronic inflammation, including antibacterial and anti-allergic effects, reduce chronic itching, and improve quality of life in the long-term management of AD.

Traditional Chinese medicine (TCM) has shown multitargeted effectiveness with a satisfactory safety profile in improving the symptom severity and quality of life of patients with AD, especially for those with refractory AD [11, 12]. According to TCM theory, damp-heat disturbing heart-mind is the most common syndrome in the pathogenesis of AD and is characterised by fatigue, shortness of breath, spontaneous perspiration or night sweating palpitation, dry mouth, attention deficits, extroversion, restlessness, insomnia, and other symptoms. Longmu Tang is composed of Os Draconis (Long Gu; 30 g/126 g), Concha Ostreae (Calcined Mu Li; 30 g/126 g), Forsythia suspensa (Lian Qiao; 15 g/126 g), Massa Medicata Fermentata (Toasted Shen Qu; 15 g/126 g), Poria cocos (Fu Ling Pi; 30 g/126 g), and Radixet Rhizonma Ephedrae (Ma Huang Gen; 6 g/126 g) (Table 1). Studies have revealed the following. (1) Os Draconis and Concha Ostreae, the key components of Longmu Tang, exert sedation-like and antipruritic effects in the treatment of AD. In addition, organic calcium in Os Draconis and Concha Ostreae can alleviate allergic symptoms [13]. (2) Forsythia suspensa inhibits *Staphylococcus aureus* on the skin surface of patients with AD [14, 15]; and (3) Poria cocos bark extract has potential as an oral immune suppressor for the treatment of AD through the generation of regulatory T cells [16]. In a previous trial, we found that the Longmu Tang granule could inhibit skin lesions and attenuate atopic itch through suppression of inflammation in AD [17]. We intend to conduct a high-quality, well-designed, randomised, placebo-controlled, double-blind clinical trial to further confirm the efficacy and safety of the Longmu Tang granule for the treatment of patients with mild-to-moderate AD.

**Table 1 Tab1:** Components of Longmu Tang granule

Chinese name	Latin name	English name
Long Gu	Os Draconis	Fossilizid
Calcined Mu Li	Concha Ostreae	Calcined concha ostreae
Lian Qiao	Forsythia suspensa	Fructus forsythiae
Toasted Shen Qu	Massa Medicata Fermentata	Toasted medicated leaven
Fu Ling Pi	Poria cocos	Tuckahoe peel
Ma Huang Gen	Radixet Rhizonma Ephedrae	Radix ephedrae

### Objectives {7}

#### Aims

The aim of this randomised controlled trial will be to evaluate the effects and safety of the Longmu Tang granule in the treatment of AD.

#### Hypothesis

This study hypothesised that the Longmu Tang granule will be able to improve the clinical symptoms, quality of life, and cognitive ability of patients with mild or moderate AD by attenuating inflammation in comparison with the placebo.

#### Objectives

To evaluate the efficacy of Longmu Tang granule in the treatment of ADTo determine whether Longmu Tang granule will improve the quality of life of patients with ADTo determine whether Longmu Tang granule will improve the cognitive ability of patients with ADTo explore the mechanism of Longmu Tang granule in the treatment of AD

### Trial design {8}

This study will be a single-centred, double-blinded, randomised, placebo-controlled clinical trial. The aim of this study is to assess the safety and effectiveness of Longmu Tang granule in treating AD with damp-heat disturbing heart-mind. The trial was registered in the Chinese Clinical Trial Registry (ChiCTR.org ID: ChiCTR2100041591).

## Methods: participants, interventions and outcomes

### Study setting {9}

This trial will be conducted at Xiyuan Hospital of China Academy of Chinese Medical Sciences. Sixty patients will be recruited for this study. All patients will be informed about the objective, approaches, potential adverse effects, and advantages of the trial. After obtaining written informed consent from the participants and their legal guardians, participants who meet the eligibility criteria will be randomly assigned to either the treatment or placebo group at a 1:1 ratio. The participants will undergo an 8-week treatment period and an 8-week follow-up.

### Eligibility criteria {10}

#### Diagnostic criteria

A diagnosis of AD will be established according to the Hanifin and Rajka diagnostic criteria. The major criteria include four clinical symptoms (e.g. pruritus, typical morphology, and distribution). The minor criteria included 32 clinical symptoms (e.g. xerosis, ichthyosis, palmar hyperlinearity, and keratosis pilaris). Participants will be diagnosed with AD if they meet three or more major criteria and three or more minor criteria simultaneously.

#### Inclusion criteria

Clinical diagnosis of ADClinical diagnosis for TCM syndromes of damp-heat disturbing heart-mindScoring Atopic Dermatitis (SCORAD) score between 0 and 50Age 6–12 yearsThose who volunteered to participate in clinical trial observation and signed the informed consent formThose compliant with treatment completion and follow-upNo intake of concomitant drugs during the observation period, except for those specified

#### Exclusion criteria

Participants with any of the following conditions will be excluded:Patients receiving antihistamine drugs, topical corticosteroids, or calcineurin inhibitors in the preceding 1 weekPatients with the presence of abnormal liver and kidney function or severe systemic diseasesPatients with other skin diseases and bacterial (fungal) infection that could interfere with the assessment of AD severityPatients with poor compliance with TCM treatmentPatients with an allergy to the ingredients in the Longmu Tang granulePatients currently participating in another clinical trial

#### Drop out criteria

Patients who voluntarily withdraw from the trial because of poor efficacy, adverse reactions, etc.Patients who are lost to follow-upPatients who use prohibited drugs in the protocol

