#### Criteria for discontinuing or modifying allocated interventions {11b}

Participants who fail to complete the study for various reasons or use prohibited drugs in the protocol, regardless of the time or reason, will be allowed to discontinue the study. Serious adverse events will be reported according to standard reporting requirements. The last recorded data for these participants will be included in the data analyses. Data obtained from participants who used prohibited drugs in the protocol will be treated as invalid. For participants who discontinue the trial, the researcher will record in detail the time and reason for discontinuation in the case report form (CRF).

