#### Safety measures

Safety measures include laboratory indices (routine blood and urine test results, and kidney and liver function test results) and adverse events. All adverse events will be tracked for 16 weeks after randomisation.

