#### Participant timeline {13}

The visit schedule for all assessments (baseline, primary outcome, secondary outcomes, exploration outcomes, and security indicators) is shown in Fig. 1. At each assessment timepoint, the same investigator will evaluate the participants. During the treatment period (i.e. from baseline to week 8), all combined therapeutic medicines will be recorded, including their name, dose, and course. Participants’ expectations of the Longmu Tang granule will be assessed at baseline. The primary outcome and CDLQI score will be evaluated at baseline and at the first, second, fourth, sixth, and last visits. Exploratory outcomes, NCT scores, and safety indicators will only be evaluated at baseline and at the last visit. Table 4 summarises the schedule of screening, enrolment, intervention, assessments, and data collection.

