#### Methods in analysis to handle protocol non-adherence and any statistical methods to handle missing data {20c}

Participants with poor adherence and a drug compliance < 80% or those who are no longer receiving medication and undergoing testing during the study will be included in the intention-to-treat analysis and excluded from the per-protocol analysis. A multiple data imputation procedure will be used to impute the missing data.

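### The protocol does not separate stopping study medicine from leaving the study, so week-8 SCORAD and exit laboratory tests are not assured in children who stop early or use a prohibited drug

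*Protocol article*

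**What the plan says.** Four parts of the protocol article decide what happens to a child who does not complete treatment as planned.

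- **Drop out criteria.** Three groups are listed: "Patients who voluntarily withdraw from the trial because of poor efficacy, adverse reactions, etc"; those lost to follow-up; and those who use a prohibited drug. The third is a drop-out by that fact alone, even if the child can still attend.
- **Section {11b}, discontinuing or modifying allocated interventions.** Children who do not complete, or who use a prohibited drug, "regardless of the time or reason, will be allowed to discontinue the study". For them, "The last recorded data for these participants will be included in the data analyses". For prohibited-drug users the rule is "Data obtained from participants who used prohibited drugs in the protocol will be treated as invalid". The time and reason for discontinuation go into the case report form. No exit assessment is named.
- **Section {20c}.** Children with compliance below 80%, and "those who are no longer receiving medication and undergoing testing during the study will be included in the intention-to-treat analysis", are left out of the per-protocol analysis. Missing data are to be multiply imputed.
- **Safety sections.** "All adverse events will be tracked for 16 weeks after randomisation". Laboratory tests are planned before and after treatment, and the Participant timeline says that "safety indicators will only be evaluated at baseline and at the last visit".

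The primary outcome is the change in SCORAD from baseline to week 8. Section {20a} promises both intention-to-treat and per-protocol analyses.

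**The concern.** An intention-to-treat comparison needs the week-8 SCORAD of every randomised child who can still be assessed, whether or not the child is still taking the granule. Here the section on discontinuing the intervention describes only discontinuing the study. A child who takes another drug because the skin is not improving is classed as a drop-out, and so is one who leaves because of an adverse reaction.

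These reasons are tied to response and to harm, so the values likely to be lost are not a random sample. Neither imputation nor a carried-forward value can verify a week-8 score that nobody took. On safety, blood and urine results come only from baseline and the last visit, so an early leaver has a post-baseline result only if someone decides to test at exit. A later analysis plan can change how missing values are handled, but it cannot recover visits that were not made.

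**Working it through.** **1. The sections side by side.**

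| Situation | Route given | Week-8 SCORAD provided for? |
|---|---|---|
| Withdraws from the trial for poor efficacy or adverse reaction | Drop-out | No; last recorded data used |
| Uses a prohibited drug | Drop-out in itself; may discontinue the study | No; data treated as invalid |
| Off medication and no longer tested | Kept in intention-to-treat, with imputation | No, by description |
| Treatment terminated after an adverse event (section {22}) | Treatment ends; participation not mentioned | Not stated |
| Stops the granule, willing to attend | No route stated | Not stated |

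The last two rows are the gap. The second is a stated rule that removes children who could be assessed.

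**2. The plan's own sample size.** Inputs from section {14}: mean reductions 15 and 6.35, SD 8.69, alpha 5%, beta 10%; two-sided testing from section {20a}.

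- Difference = 15 − 6.35 = 8.65; standardised, 8.65 / 8.69 = 0.995.
- Two-sample t-test with the noncentral t distribution: 23 per arm, 46 in all, power 91.0%. This reproduces the stated figure.
- Allowance for 20% loss: 46 / 0.8 = 57.5, so 58, against the stated 60. The plan thus provides for about 0.20 × 60 = 12 children lost.

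The numbers are adequate for power. The question is which children are lost.

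**3. Illustration of bias.** These assumptions are mine, not the protocol's: normally distributed improvements with SD 8.69 in each arm, the children with the smallest improvement leave, and completers only are compared. If the lowest fraction p of an arm leaves, the mean of those remaining rises by

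shift(p) = SD × φ(z_p) / (1 − p),

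where φ is the standard normal density and z_p its p-quantile.

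- p = 0.1: 8.69 × 0.1755 / 0.9 = 1.69
- p = 0.2: 8.69 × 0.2800 / 0.8 = 3.04
- p = 0.3: 8.69 × 0.3477 / 0.7 = 4.32
- p = 0.4: 8.69 × 0.3863 / 0.6 = 5.60

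Observed difference = 8.65 + shift(active) − shift(placebo). With 30 per arm, each row below loses 12 children in total:

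| Loss, placebo / active | Children | Observed difference |
|---|---|---|
| 20% / 20% | 6 / 6 | 8.65 (no bias) |
| 30% / 10% | 9 / 3 | 6.03 |
| 10% / 30% | 3 / 9 | 11.27 |
| 40% / 0% | 12 / 0 | 3.05 |
| 0% / 40% | 0 / 12 | 14.25 |

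The shift does not depend on the true difference. With no true effect, 10% loss on placebo and 30% on active would produce an apparent benefit of about 2.6 points.

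**4. Weaker selection.** If leaving is only correlated 0.5 with the outcome, each shift halves. The 2.62-point shift becomes 1.31, so the two 30%/10% splits give 8.65 − 1.31 = 7.34 and 8.65 + 1.31 = 9.96.

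**The case against.** A reader might infer that stopping the granule ends participation, so that week-8 SCORAD and end-of-treatment safety tests are never collected in these children. The documents do not say that:

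- The first drop-out criterion concerns children who withdraw from the trial itself, not those who only stop the medicine.
- Section {11b} is permissive: children are allowed to discontinue.
- Section {22} speaks of terminating the treatment and does not mention removal from the trial.
- Section {20c} names a category for analysis. It does not say that every child off medication stops being tested.
- Adverse-event tracking to 16 weeks has no exception for leavers, so it may be the follow-up that is sought; it is not shown to be contradicted.
- A test after treatment, or at the last visit, could be done at exit.

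SCORAD is also scored at interim visits, so many leavers would have some post-baseline value. Multiple imputation could recover part of what is lost, so a completers-only comparison overstates the problem to that extent. A journal article may leave early-termination procedures to the full protocol, and the contents of Fig. 1 and Table 4 were not available for this review.

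All of this stands against the strong reading. It does not remove the narrower point. Prohibited-drug use as a drop-out, exit from the study as the only stated route, and invalid status for those children's data are rules written in the article, not details left out of it. The interim values also help little for prohibited-drug users if their data are set aside as invalid.

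**Conclusion.** The point holds in this form: the protocol does not distinguish stopping study medicine from leaving the study, and followed as written it is likely to lose week-8 SCORAD, for reasons linked to outcome, in children who could still be assessed. That weakens the intention-to-treat analysis it promises. Exit laboratory tests are not assured; the text does not show that they are lost.

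The size depends on how uneven the loss is between arms. Under the stated assumptions, equal loss produces no bias. The planned 20% overall loss, split 30% and 10%, moves the difference by about 2.6 points in either direction, or about 1.3 with selection half as strong. The all-in-one-arm extreme is about 5.6 points. The protocol does not show which pattern to expect.

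A reader might also remove the worst 20% from placebo alone, obtain 8.65 − 3.04 = 5.61, and note that it falls below the minimal clinically important difference of 8.7. That requires loss in one arm only, which is 6 of 60 children and not the planned 20%, and the planned difference of 8.65 is itself already below 8.7.

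This should be corrected because it is cheap and cannot be repaired after the visits are missed. It does not invalidate the design or the sample size.

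**What to change.** Change data collection only; which drugs are prohibited, and who may stop treatment and when, stay as they are.

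1. In the Drop out criteria and section {11b}, distinguish (a) stopping study medicine or using a prohibited drug from (b) withdrawing consent to follow-up or being lost. Only (b) ends data collection.
2. State that children in (a) stay on the existing schedule: SCORAD and CDLQI at the remaining visits, including week 8 and the end of the 8-week follow-up, adverse events to week 16, and the planned end-of-treatment tests.
3. If a child will not return, do the planned end-of-treatment SCORAD, CDLQI, NCT and blood and urine tests at the time of stopping.
4. Reword section {20c} so that being off medication and being no longer tested are separate categories. Reconcile its imputation rule with the last-recorded and invalid-data rules in {11b}.
5. Align Safety measures, Safety assessment, the Participant timeline {13} and section {22}, and say what the last visit means for an early leaver.

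The cost is protocol wording and some effort to retain children who are off medicine. The visits and tests are already planned, and section {18b} already offers examinations free of charge.

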#### Public and patient involvement

Two AD patients in [name] clinic have provided an idea for us to place posters in the hospital areas (e.g. the outpatient hall) to recruit patients prior to the trial. The patients will not be involved in other parts of the trial design, such as the recruitment or conduct of this study.

#### Who will take informed consent? {26a}

The researchers will design the questionnaire, recruit patients, and conduct the study. The participants and their guardians will complete the informed consent form if they would like to participate in the study. The informed consent form will explain the purpose, procedure, potential benefits, and risks of the trial.

#### Additional consent provisions for collection and use of participant data and biological specimens {26b}

Prior to obtaining informed consent, we will confirm with the participants the right to use their data, which indicates that the participants’ data will be shared with the other relevant authorities. The trial will not involve collection and use of biological specimens.

### Interventions

#### Explanation for the choice of comparators {6b}

The Longmu Tang placebo granule was selected as the comparator to assess the effects and safety of Longmu Tang granule and to minimise bias.

#### Intervention description {11a}

In the Longmu Tang granule group, participants will be allocated to receive the Longmu Tang granule (9.8 g/sachet) orally with 50 mL of warm water twice a day for 8 weeks. Active granules, each containing 9.8 g of Longmu Tang, are equivalent to 126 g of crude medicine. The placebo granule is composed of 5% crude Longmu Tang and 95% starch with a similar appearance and smell to the Longmu Tang granule. Patients in the control group will take the placebo orally at the same time as those in the Longmu Tang granule group. Both Longmu Tang granule and placebo granules with similar labels and packaging will be provided by Beijing Tcmages Pharmaceutical Co., Ltd. Based on the quality control analysis, the Longmu Tang granule used in the trial should meet the Chinese Medicine Standards of the State Food and Drug Administration.

